### Masking

Due to the nature of the intervention, it is not possible to mask participants and delivery agents to the treatment allocation. However, outcome assessments will be masked/blinded, as all outcome measures will be administered by trained research assessment teams, who will be non-residents of the study area, independent of the intervention and blinded to treatment allocation of the participants. Furthermore, participants will be instructed not to disclose any information about the intervention or the delivery agent assessment team. The intervention implementation team and outcome assessment teams will not have any interactions during the trial since there will be separate locations and administrative management.

## Monitoring for adverse events

### Serious adverse events (SAEs)

A serious adverse event (SAE) is a serious medical or psychological issue that happens to a participant, even if it is not caused by the study. The following events will be considered potential serious adverse events (SAEs) and will be reported accordingly. This list is not restrictive; any incident reported will be assessed against the defined seriousness criteria and reported if deemed appropriate. Potential SAEs include (1) death of a participant from any cause; (2) any suicide attempt; (3) observed incidents of domestic violence or victimization involving the participant; (4) hospital admission due to psychiatric issues; (5) hospital admission due to a serious medical emergency; (6) miscarriage, stillbirth, or loss of a child; and (7) any other event that meets the seriousness criteria as outlined in the protocol (or is otherwise deemed medically significant by the site investigator).

The reported adverse event will be assessed for seriousness by an independent psychiatrist based at the site, who will evaluate the event, determine its relevance to the trial, and advise on any necessary actions. If the event is judged to be related to the trial. 

Principal Investigator (PI) will report it to both the relevant ethics committees and the Data and Safety Monitoring Board (DSMB) within 72 h. Additionally, all SAEs regardless of relatedness will be compiled and reported in a blinded format every 6 months to both the Yale Institutional Review Board (IRB) and the DSMB.

### Other adverse events (OAEs)

In addition to the SAEs, other adverse events (OAEs) will be reported to the Institutional Review Board (IRB). This includes (1) any serious or non-serious adverse event that is unanticipated and indicates that the research places participants or others at greater risk of harm than was previously known or recognized, (2) information that indicates an adverse change to the risks or potential benefits of the research or allegation of non-compliance with protocol requirements, (3) breach of confidentiality, (4) incarceration of a participant in a protocol not approved to enroll prisoners, (5) sponsor-imposed suspension for risk, (6) complaint of a participant if it indicates unexpected risks or cannot be resolved by the research team, (7) any protocol deviation or violation that harmed participants or others, (8) that indicates participants or others may be at increased risk of harm, (9) or that compromises the integrity of the research data, (10) any protocol changes made without prior IRB approval to eliminate apparent immediate harm and any safety reporting requirements specified by the IRB as a condition of approval.

Other Adverse Events (OAEs) will be documented if identified by the delivery agents—peers in the intervention arm or Lady Health Workers (LHWs) in the Enhanced Usual Care (EUC) arm—or by peer supervisors, and will be addressed. The research team will follow the guidelines of the Yale University IRB and the National Bioethics Committee of Pakistan regarding unanticipated problems that pose risks to participants or others.

### Training and supervision of peer mothers

Peer mothers’ selection was co-developed in collaboration with the CAB and informed by the research team’s extensive experience implementing task-shifting mental health interventions in Pakistan. Peer mothers will be lay women with no formal mental health training who have demonstrated an interest in supporting other women in their communities. Eligibility criteria include being aged 18 years or older, regardless of marital status; fluency in Urdu; completion of at least matriculation education (Grade 10); residence in the same or nearby communities as trial participants; and an intention to remain in the study area for the full duration of the follow-up period. Peer mothers will complete a three-phased training and supervision process. Phase 1 will consist of a 4-day, in-person training delivered by Pakistani female Peer Clinical Psychology Supervisors with master’s-level training in psychology. This phase emphasizes interactive learning approaches, including group discussions and role-playing exercises, and covers core content areas such as the KPZ intervention components, ethical conduct and confidentiality, managing difficult or distressing situations, and the identification, documentation, and reporting of serious adverse events (SAEs).

Phase 2 will involve 6–7 weeks of supervised field-based training, during which peer mothers deliver KPZ sessions to practice cases. All sessions will be either directly observed or audio-recorded and reviewed by peer supervisors. During this phase, peer mothers will participate in weekly one-on-one supervision meetings focused on structured feedback, skills development, and competency assessment.

Phase 3 will include ongoing group-based supportive supervision with all peer mothers throughout the intervention period. Supervision is grounded in a supportive supervision model and focuses on addressing implementation challenges through role-play and problem-solving, reinforcing effective practices, maintaining peer mothers’ motivation and well-being, and conducting periodic competency assessments to ensure fidelity and quality of delivery.

### Evaluating competency of peer mothers delivering KPZ

Upon completion of training, peer mothers will undergo competency assessments using structured, standardized role-playing exercises. The 19-item Enhancing Assessment of Common Therapeutic Factors tool ENACT [33] will be used to assess peer mother competence at the initial stage (baseline) of KPZ delivery. A minimum score of 70% is required for a peer mother to qualify to deliver the intervention. Peer mothers will be re-assessed at midline and endline during monthly supervision sessions through role-plays based on scripted scenarios. Only those peer mothers who consistently meet the required competency levels will be selected to deliver KPZ in the trial. During assessments, trainers will conduct one-on-one role-plays with each peer mother while the remaining peer mothers observe. Peer mothers will first reflect on their own performance, followed by detailed feedback from trainers. If a peer mother scores below the required competency threshold at any point, she will receive refresher training to regain the necessary competency before proceeding.

## Measures

Table 1 below summarizes all primary and secondary outcome measures and Table 2 below summarizes all implementation outcome measures, including their descriptions and assessment time points.

**Table 2 Tab2:** Implementation outcome measures

Implementation outcomes		
Outcome measure	Measure description	Time frame
Trial feasibility		
Percent eligible participants who consent	Proportion of individuals who met eligibility criteria and provided informed consent to participate in the study	At recruitment
Percent of consented participants who started intervention	Proportion of participants who initiated at least one KPZ intervention session after consenting	6 months
Percent of participants who completed KPZ safety card	Proportion of enrolled participants who completed the KPZ safety card component	6 months
Percent of participants who completed one brief contact follow up session	Proportion of enrolled participants who completed at least one brief follow-up contact session	6 months
Percent of participants who dropped out of KPZ intervention	Proportion of participants who discontinued participation prior to completing the intervention	3 months and 6 months
Fidelity		
Median number of sessions completed	Median number of sessions completed by participants	6 months
Feasibility		
Feasibility of Implementation Measure (FIM)	FIM is a 4-item feasibility scale [41]. The scale was culturally adapted to fit the study and Urdu language	6 months post-enrollment
Acceptability		
Acceptability of Implementation Measure (AIM)	AIM is a 4-item Acceptability scale to assess perspectives on implementation [41]. The scale was culturally adapted to fit the study and Urdu language	6 months post-enrollment
Appropriateness		
Intervention Appropriateness Measure (IAM)	IAM is a 4-item appropriateness scale [41]. The scale was culturally adapted to fit the study and Urdu language	6 months post-enrollment
Cross cutting across FIM/AIM/IAM		
Individual qualitative interviews with intervention mothers	We will conduct qualitative interviews with trial participants to explore their perspectives on the intervention’s content and delivery, aiming to elicit insights into its feasibility, acceptability, and perceived mechanisms of change.”	Baseline and 6 months post-enrolment
Longitudinal periodic reflections with peer mothers and peer supervisors	We will conduct periodic reflections with peer mothers and peer supervisors to regularly check in on the progress of P-SuPP implementation. These reflections will provide space to discuss, document, and reflect on important events, activities, and changes occurring throughout the course of implementation	two elicitations per peer mother, one in first half and one in second half of implementation
Knowledge, attitudes, self-efficacy		
Knowledge, Attitudes, and Confidence (KAC)	The KAC is a 30-item questionnaire developed from our formative co-design research that assesses implementing agent (e.g., peer mother) implementation domains of confidence (11 items), attitudes (acceptability, appropriateness, perceived benefit) (13 items), and knowledge (6 items) in implementing the elements of KPZ with the mother directly and within her social milieu (e.g., family engagement). Items will be responded to with a 4-item Likert scale with responses ranging from 'none of the time' to 'all of the time'. Higher scores indicate more confidence, more positive attitudes, and more knowledge of KPZ intervention components and suicide myths	6 months post- enrollment

### Primary clinical outcomes

Suicidal ideation severity will be assessed using the Beck Scale for Suicidal Ideation (BSSI) [34, 35], while the presence of any suicidal behaviors and attempts will be measured using the Columbia Suicide Severity Rating Scale (C-SSRS) [36]. Both will be administered at baseline and 6-month post-recruitment.

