### Objectives of the study

To evaluate the feasibility of the peer-delivered KPZ intervention for reducing suicidal ideation, behaviours, and attempts among adult married women in the peri-rural areas of Islamabad capital Territory (ICT), Pakistan.To evaluate the preliminary effectiveness of the peer-delivered KPZ intervention in reducing suicidality and improving mental well-being among adult married women, compared with Enhanced Usual Care (EUC), at 3- and 6-months post-recruitment in Pakistan.To assess the acceptability and appropriateness of the KPZ intervention and its implementation among peer mothers and participants.To evaluate the appropriateness of KPZ and trial safety procedures, from the perspectives of married women, peer mothers, trainers, and primary health care providers.To assess treatment adherence among adult married women receiving peer-delivered KPZ intervention sessions.To assess the preliminary fidelity of KPZ intervention implementation.

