## Assessments

### Baseline assessment

All baseline assessments will be conducted by trained members of the research team who are blinded to participants’ allocation status. Baseline data will include sociodemographic characteristics, including age, marital status, reproductive history (including previous pregnancies and miscarriages), educational attainment, and employment status.

Baseline assessments will also measure the severity of suicidal ideation, depression, and anxiety; perceived social support; suicide-related cognitions; exposure to intimate partner violence (IPV); moral injury; and health services utilization in the 6 months preceding enrollment. Detailed descriptions of the assessment instruments used for each construct are provided in Table 1.

**Table 1 Tab1:** Primary and secondary outcome measures

Primary outcome measures		
Outcome measure	Measure description	Time frame
Beck's Scale for Suicidal Ideation (BSSI)	Suicidal ideation severity will be measured using the Urdu validated BSSI [34, 35]. The BSSI is a 19-item self-report instrument that assesses the intensity of suicidal thoughts, attitudes, and behaviors over the past 2 weeks. Each item is rated on a 3-point scale (0–2), with total scores ranging from 0 to 38; higher scores indicate greater severity of suicidal ideation	baseline and 6 months post-enrollment
Suicidal behaviors measured by Columbia Suicide Severity Rating Scale (C-SSRS)	Suicidal behaviors and attempts will be assessed using the C-SSRS [36]. The C-SSRS captures self-reported suicide attempts, aborted attempts, and interrupted attempts using dichotomous (yes/no) items. Any endorsement of these behaviors will be coded as a positive suicidal behavior outcome	baseline and 6 months post-enrollment
Secondary outcome measures		
Outcome measure	Measure description	Time frame
Patient Health Questionnaire—9 item (PHQ-9)	Depressive symptoms will be measured using the Urdu validated PHQ-9 [37], a 9-item self-report instrument assessing the frequency of depressive symptoms over the past 2 weeks. Items are rated on a 4-point scale ranging from 0 (not at all) to 3 (nearly every day), with total scores ranging from 0 to 27; higher scores indicate greater severity of depressive symptoms	Baseline, 3 and 6 months post-enrollment

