### Follow-up assessments

All participants will be followed up at 3- and 6-months post-recruitment by trained research staff blinded to allocation status of the participants. Follow-up assessments will reassess suicidal ideation, depression, anxiety, perceived social support, suicide-related cognitions, intimate partner violence, moral injury, and health services utilization since the previous assessment. A subsample of purposively selected trial participants will be approached at 1 month and/or 6-months post-enrollment to qualitatively elicit experiences related to their suicidality, the trial, and the health system.

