### Quantitative analysis

Data will be analyzed using Stata [44] and R [45], following CONSORT guidelines relevant extensions for cluster-randomized and pilot-feasibility trials. Participant flow will be presented using CONSORT diagrams, including numbers screened, eligible, randomized, and analyzed for the primary outcomes. All clinical and feasibility analyses will be conducted based on the intention-to-treat (ITT) principle, where all randomized participants will be included in the analysis in the group to which they were originally assigned, regardless of the treatment they actually received or any protocol deviations. For continuous measures, means (standard deviations) or medians (interquartile ranges) will be reported as appropriate; for categorical outcomes, counts and proportions will be presented.

At baseline, demographic characteristics will be summarized by study arm to assess randomization balance and to facilitate comparison of the distribution of potential confounding factors. For follow-up assessment at 3 and 6 months, clinical outcome measures will likewise be reported by trial arm using summary statistics including means, standard deviations, and interquartile ranges. This consistent reporting structure allows for arm-wise evaluation of outcomes across all time points.

Means and frequencies will be used to describe baseline characteristics, participation rates in the study procedures, instrument/item response rates, and engagement with the peer-mother-delivered intervention. Means and frequencies for each suicide-related outcome (e.g., CSSR-S and BSSI) and secondary outcomes (e.g., PHQ-9, GAD-7) will also be calculated at each assessment point.

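### BSSI and C-SSRS, the two primary clinical outcomes, are scheduled only at baseline and 6 months, but the objective and analysis text call for suicidality results at 3 months

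*Protocol article*

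**What the plan says.** **Where the primary outcomes are defined.** The section Primary clinical outcomes names the BSSI for severity of ideation and the C-SSRS for suicidal behaviours, and states: "Both will be administered at baseline and 6-month post-recruitment". In Table 1 the time frame for each of the two is "baseline and 6 months post-enrollment". All four secondary scales in Table 1 (PHQ-9, GAD-7, MSPSS, MSRI) are scheduled at baseline, 3 and 6 months.

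**Where 3-month results are expected.**
- Objectives of the study, second objective: KPZ is to be evaluated "in reducing suicidality and improving mental well-being among adult married women", "compared with Enhanced Usual Care (EUC), at 3- and 6-months post-recruitment in Pakistan".
- Follow-up assessments: "All participants will be followed up at 3- and 6-months post-recruitment by trained research staff". On content: "Follow-up assessments will reassess suicidal ideation, depression, anxiety, perceived social support, suicide-related cognitions", followed by further constructs. No instrument is named, and suicidal behaviours are not listed.
- Quantitative analysis: clinical outcome measures are to be reported by arm at 3 and 6 months. Means and frequencies for the C-SSRS and BSSI, named in the same sentence as the PHQ-9 and GAD-7, "will also be calculated at each assessment point".

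**How the behaviour outcome is coded.** Table 1 limits the C-SSRS outcome to self-reported attempts, aborted attempts and interrupted attempts, and adds: "Any endorsement of these behaviors will be coded as a positive suicidal behavior outcome". No rule for death is given there.

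**The concern.** The sections that define the primary outcomes give one follow-up time. The sections that set the objective and the reporting give two. A team working from Table 1 will not collect what the second objective and the analysis section promise. A team working from the Follow-up assessments section may collect a 3-month ideation measure that the outcome definitions do not recognise.

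Two things are at stake. First, a between-arm comparison of suicidality at 3 months would have no primary measure behind it. By the session schedule in KPZ intervention arm (five sessions in month 1, four biweekly, then three monthly), about nine of the 12 sessions fall in roughly the first three months, so month 3 closes the intensive phase. Because the BSSI looks back only two weeks, a 6-month score says nothing about severity at that time.

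Second, the mixed models rely on missing at random and on each participant's available data. With only one post-baseline occasion, a woman without a month-6 visit has only her baseline value of that outcome from which anything could be recovered. This matters in a pilot whose stated purposes include preliminary effect sizes and the ICC of the primary outcomes.

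**Working it through.** The protocol states no figure to reproduce: the sample size rests on pilot guidance, and no effect size, SD or event rate is given. The check sets the sections side by side and adds simple counts.

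**1. Sections compared**

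| Section | BSSI / ideation at 3 months? | C-SSRS / behaviours at 3 months? |
|---|---|---|
| Primary clinical outcomes | no | no |
| Table 1, primary rows | no | no |
| Second objective (suicidality) | yes | yes, if suicidality covers behaviours |
| Follow-up assessments | yes for ideation, instrument not named | not listed |
| Quantitative analysis | yes | yes |

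The conflict is firmest for ideation, where three sections contradict two. For the C-SSRS it rests on the second objective and the analysis section only.

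**2. Scheduled observations per primary outcome** (50 women, Sampling procedures)
- Baseline and 6 months: 50 × 2 = 100.
- Baseline, 3 and 6 months: 50 × 3 = 150.

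**3. Women with no post-baseline primary value**
- Table 3 sets Go at 70% retained. With 50 recruited, 50 × (1 − 0.70) = 15 may have no month-6 visit.
- Under the current schedule all 15 lack any post-baseline BSSI or C-SSRS.
- If x of the 15 were seen at month 3, adding the scales would leave 15 − x without a post-baseline value. The documents do not give x, so the gain ranges from 0 to 15 women. Fifteen is an upper bound, and the trial itself aims to retain all 50.

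**4. Secondary note: one suicide death in an arm of 25.** Event counts are assumed, because none is given. With k other women positive, the arm proportion is k/24 if the death is left out and (k + 1)/25 if it is counted.

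| k (assumed) | Death left out | Death counted | Difference |
|---|---|---|---|
| 0 | 0/24 = 0.0% | 1/25 = 4.0% | 4.0 points |
| 2 | 2/24 = 8.3% | 3/25 = 12.0% | 3.7 points |
| 4 | 4/24 = 16.7% | 5/25 = 20.0% | 3.3 points |

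This assumes that everyone else in the arm is observed at month 6.

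**The case against.** **A single 6-month primary time point is a legitimate choice, and the two places that define the outcomes agree.** True. The phrase about each assessment point can also be read as each point at which that measure is scheduled. But that reading does not reach the second objective, which attaches 3 months to suicidality, or the sentence reporting clinical outcomes at 3 and 6 months without separating primary from secondary.

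**Some 3-month information on suicidality will exist.** A reader might infer that nothing can be said about month 3. The documents do not support that: PHQ-9 item 9 is the trial's own entry criterion for ideation, the PHQ-9 is given at 3 months, and so is the MSRI on suicide-related cognitions. But Table 1 assigns ideation severity to the BSSI and uses the PHQ-9 for depressive symptoms, and neither scale measures suicidal behaviour. It is the primary measures that are absent.

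**The analyses are exploratory.** This stands. The Limitations section says that the trial is not designed to assess suicide-related outcomes, and none of the three progression criteria uses BSSI or C-SSRS. That limits the consequence but does not remove the contradiction, because the same article names these outcomes as primary.

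**Deaths.** A reader might infer that the plan codes suicide deaths as missing. No section says so. That follows only by combining the self-report definition in Table 1, the Loss to follow-up rule (which does not mention deaths) and the missing-at-random models. A full protocol or SAP, not shown, may settle it. Deaths and attempts are recorded as serious adverse events in any case. What stands is narrower: the published definition gives a suicide death no route into the behaviour outcome.

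**Conclusion.** The schedule contradiction holds and needs correcting. As written, neither primary clinical measure can answer the 3-month part of the second objective, and each primary outcome has 100 scheduled observations where the objective and analysis text imply 150. At the 70% retention limit, at most 15 of 50 women would have no post-baseline primary value. That bound assumes full recruitment and includes women lost before month 3, whom a 3-month assessment would not help.

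The point about deaths is a secondary clarification, not a demonstrated error. One uncounted suicide death would lower an arm's proportion by about 3.3 to 4.0 percentage points, under assumed counts of 0 to 4 other positive women among 25.

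The effect is on the estimates, their interpretation and the planning of the definitive trial. No powered test and no progression criterion depends on it.

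**What to change.** Choose one of two routes and make every section agree.

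1. **Add the measures.** Give BSSI and C-SSRS at the existing 3-month visit to women who have not yet passed it, and correct Table 1 and Primary clinical outcomes. Keep the BSSI's two-week window; ask the C-SSRS for the period since the last visit. The cost is two short scales at a visit already held, and missing 3-month values for women already past it.
2. **Correct the wording.** If route 1 is no longer practical, limit the suicidality part of the second objective, and the matching text in Follow-up assessments and Quantitative analysis, to 6 months. This costs only wording, but gives up the 3-month comparison on the primary measures.

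Route 2 may be the only one left. Recruitment was planned over 1.5 years, and the Study design section names May 2024. Even if that date marks the start of recruitment, planned enrolment would end about November 2025 and the last 3-month visit would fall about February 2026, before publication in June 2026. The article describes the trial as ongoing, so the team should check how many women have still to reach month 3.

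In the same amendment, state that a death by suicide counts as a positive behaviour outcome. Report attempts documented only as serious adverse events separately, or as a sensitivity analysis. Do not merge them into the main outcome: KPZ women have 12 sessions with peer mothers trained to identify and report such events and EUC women do not, so detection may differ by arm, and blinded classification would not correct that.
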